### Measures

The primary endpoints to assess intervention impact are STI incidence and IPV perpetration. To assess STI incidence, we are using Qiagen Artus CT with in-house PCR to detect CT, Trichomonas vaginalis Real-TM test to detect TV, and 16 s rDNA PCR to detect NG. For the follow-up testing at 30 months we are using Multiplex PCR to detect CT and NG. Study participants who are identified with NG, CT, or TV are offered free treatment by a study clinician at the study site according to the standard of care in Tanzania specifically NG (Ceftriaxone), CT (Doxycycline), TV (Metronidazole). IPV perpetration is assessed using an adapted version of the World Health Organization violence against women instrument [63]. This tool measures psychological, physical, and sexual IPV perpetration. Participants are asked whether they have perpetrated any of 13 behaviorally specific violent acts, including 4 psychological acts, 4 physical acts and 3 sexually violent acts, against a current or former sexual partner. For those who say yes to ever having perpetrated a specific act of violence, they are asked to report how many times they perpetrated that act in the last 12 months. Response options included never, once, 2–3 times, 4–10 times, and more than 10 times. The responses to the frequency of physical and sexual IPV perpetration within the last 12 months are dichotomized such that a 0 represents no sexual/physical IPV perpetration and a 1 represents at least 1 act of sexual or physical IPV perpetration within the last 12 months. We are measuring gender norms with the gender-equitable men’s scale [36], as well as hope [64], future orientation [65], and perceived social support as mediators of the intervention’s effects. We are measuring camp-level social cohesion using five items adapted from a measure of social cohesion developed by Sampson, Raudenbush & Earls [66]. For example, participants are asked how strongly they agree with statements like “people in my camp are willing to help each other” and “the members of my camp share the same values.” In addition, we are collecting data on all social ties within each camp at multiple waves of data collection. We are using these complete network data to assess whether our intervention is mediated through the transformation of social network structures (e.g. structural cohesion [67]). Finally, we are also looking at HIV risk behaviors as secondary endpoints including unprotected sex, sexual partner concurrency, alcohol and other substance use.

### Retention

Young men in this urban context are highly mobile, often moving for work-related opportunities. A number of strategies are employed to maximize participant retention through the life of the study. (1) Camp rosters containing member names and phone numbers were collected before the baseline assessment, and are updated with camp leader assistance before follow up data collection. (2) Phone numbers of participant family members and close friends are collected at baseline to assist in locating camp members difficult to track down at follow-up. (3) Bi-annual CAB meetings are held to maintain connection with camp leadership and check-in on camp membership. (4) For any respondent who leaves the camp and/or moves, we are using additional strategies such as finding out if they are still living around Dar es Salaam to contact them and encourage them to return for interviews, including providing additional funds for transport if they are located far from the field offices within Dar es Salaam.

### Qualitative sub-studies

We are conducting qualitative sub-studies during the study to follow-up in more depth on a few issues of particular interest to our study team. Our first qualitative study is focused on the *role of camps in men’s perpetration of violence.* This qualitative study is designed to understand more about the role that social networks within camps play in influencing men’s perpetration of violence against their female partners. In this sub-study, 20 men who report at least one episode of violence with their sexual partner in the past 12 months are selected for interviews. The interviewers ask men about how members of their camp talk to each other about relationships, and conflicts within relationships. They also ask for more information about the conflicts that selected participants have had with their partners to try to understand how they talked to camp members about these relationship conflicts. We conduct two interviews with each man. The second qualitative sub-study is focused on *camp leadership and microfinance uptake.* As we have implemented the intervention we have become increasingly aware of the important role that some camp leaders play in the functioning and decisions that are made within the camps. We will select 3 camps that took loans and 3 camps that did not and conducted semi-structured interviews with 2 leaders and 3-4 members per camp for a total of 30-36 interviews. We want to understand more about the strategies that camp leaders use to lead their camps, and how influential camp leaders are in the decisions of camps members regarding the uptake of loans. All qualitative interviews are conducted in Swahili by trained qualitative interviewers, audio recorded, transcribed, and translated for data analysis.

### Sample size determination

The choice of 60 camps randomized into two groups is based upon evidence generated in our previous study and likely incidence estimates available from published studies with similar populations in Tanzania and other countries in Africa [10, 68]. We estimated average camp sizes of 26.4 men and expected to successfully enroll approximately 80 % of these men into our trial at baseline. 90 % of the men were expected to be sexually active at baseline. Any STI incidence (NG, CT, or TV) was used as the primary outcome measure and sexual and/or physical IPV perpetration was used as the primary behavioral outcome measures. Based upon our previous study we computed camp intraclass correlation (ICC) estimates between 0.00 and 0.01 for sexually transmitted diseases and 0.032 for behavioral measures. Given anticipated average camp sizes and ICC estimates we inflated sample size estimates assuming simple random sampling with design effects ranging from 1.4 to 2.3. All sample estimates assumed an attrition of 20 %. Given a sample size of 890 sexually active males and 999 total males in 60 camps at our 30-month assessment, we will have 80 % power (2-sided, α = 0.05) to detect protective effects of the intervention (OR) of .57 for STI incidence and .65 for perpetration of sexual or physical IPV among sexually active men. Statistical power to detect mediation is expected to be high based on the simulation results of Fritz and MacKinnon where a total sample size of 539 was sufficient for .80 power to detect the most conservative simulated mediation effect.

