#### Selection and random assignment of camps for the trial

Due to the density of geographically proximal camps (see Fig. 2), we used a three step, probability based sampling method that reduced the possibility of contamination effects to randomly select 60 eligible camps in to the trial: (1) field staff familiar with the physical geography of wards and camps assigned geographically proximal camps to groups containing between 1–6 camps on ArcGIS generated maps; (2) probability proportionate to size with minimal replacement sampling of groups was conducted using SAS Survey Select Procedure; (3) simple random selection of camps within groups selected was completed. By using minimal replacement, groups containing greater numbers of camps with high membership numbers could be selected more than once. In such an instance, the number of times a group was selected equaled the number of camps selected randomly from that group. The 60 randomly selected camps were first randomized into two sets of 30 camps. Multiple camps selected from within the same geographically proximally group were assigned to the same set. Treatment condition of these two sets was then randomly, and transparently, assigned at a CAB meeting following completion of baseline data collection. At the CAB meeting, the two sets were assigned numbers one and two. Papers with these numbers were then put in separate but identical balloons, and three other papers that stated “try again” in three other identical baloons. The CAB decided that the first number to be selected would be assigned to the intervention condition. One CAB member was selected to be the one to randomly pick and pop the balloons until a number was found.

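### The stated 80% power for an IPV odds ratio of .65 is not attainable with 890 sexually active men and the protocol's own design effects; the best case is about 77%

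*Protocol article*

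**What the plan says.** All the figures are in the protocol article under Sample size determination, except the allocation.

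- Analysed sample: "Given a sample size of 890 sexually active males and 999 total males in 60 camps at our 30-month assessment". Attrition is already allowed for: "All sample estimates assumed an attrition of 20" per cent.
- Error rates: "we will have 80 % power (2-sided, α = 0.05").
- Clustering: "camp intraclass correlation (ICC) estimates between 0.00 and 0.01 for sexually transmitted diseases and 0.032 for behavioral measures".
- Inflation, attributed to the anticipated camp sizes and those ICCs: "we inflated sample size estimates assuming simple random sampling with design effects ranging from 1.4 to 2.3".
- IPV effect: an odds ratio (OR) of ."65 for perpetration of sexual or physical IPV among sexually active men" (the decimal point stands just before the quoted words).
- Allocation, from Selection and random assignment of camps: "The 60 randomly selected camps were first randomized into two sets of 30 camps".

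The section gives no control-arm IPV prevalence for the calculation.

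**The concern.** IPV perpetration is one of the two primary endpoints (Primary hypothesis; Measures), and .65 is the only benchmark the article gives for the size of IPV effect the trial can detect. If the sample size and design effects printed beside it cannot deliver that benchmark, the trial is less sensitive on this endpoint than it says. A null IPV result could then be read as stronger evidence against an effect of that size than the data can supply. The design-effect range also looks too high for the ICCs it is said to come from, so a reader cannot tell which value was applied to which endpoint.

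**Working it through.** **Inputs.** N = 890 sexually active men, split equally by arm (445 each, following 30:30 camps); two-sided 5%; OR 0.65; design effect (DEFF) 1.4 to 2.3; behavioural ICC 0.032; average camp size 26.4. Control prevalence p1 is not given, so it was scanned from 5% to 95% and the value most favourable to the protocol was taken. The result is an upper bound that needs no outside figure.

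**Formulas.**
- Effective men per arm: n = (N/2)/DEFF.
- Intervention prevalence: p2 = 0.65·p1/(1 − p1 + 0.65·p1).
- Power = Φ{[|p1 − p2|·√n − 1.96·√(2·p̄(1 − p̄))]/√[p1(1 − p1) + p2(1 − p2)]}, with p̄ = (p1 + p2)/2.

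**Trying to reproduce 80% with 890 men.** The most favourable prevalence is about 55%, where p2 = 0.4427 and p̄ = 0.4964. At DEFF 1.4, n = 445/1.4 = 317.9. The numerator is 0.1073 × √317.9 − 1.3859 = 1.9126 − 1.3859 = 0.5267. Dividing by 0.7030 gives 0.749, so power is 77.3%. Unpooled, log-odds and arcsine versions give 77.0% to 77.7%.

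| DEFF | Source | Maximum power, 890 men | OR detectable at 80%, best case |
|---|---|---|---|
| 1.4 | stated minimum | 77.3% | 0.64 |
| 1.44 | 1 + (890/60 − 1) × 0.032 | 76.1% | 0.636 |
| 2.3 | stated maximum | 56.0% | 0.565 |

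**Design effect that would be needed.** Without clustering, 80% power needs at least about 340 men per arm (680 in total). The ceiling is therefore 890/680 ≈ 1.31, below the stated minimum. At DEFF 1.4 the requirement is 680 × 1.4 = 952 men.

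**Using all 999 men.** The ceiling becomes 999/680 ≈ 1.47. Maximum power is 81.9% at DEFF 1.4, where 80% is reached only for control prevalences of roughly 45% to 65%. It is 80.7% at DEFF 1.44. The ICC of 0.032 with 999/60 = 16.65 men per camp gives DEFF = 1 + 15.65 × 0.032 = 1.50 and a maximum of 79.2%.

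**Rebuilding the design-effect range**, DEFF = 1 + (m − 1)·ICC:

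| Men per camp, m | ICC 0.00 to 0.01 (STI) | ICC 0.032 (behavioural) |
|---|---|---|
| 14.8 (890/60) | 1.00 to 1.14 | 1.44 |
| 26.4 (full camp) | 1.00 to 1.25 | 1.81 |

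A value of 2.3 needs an ICC of 1.3/25.4 = 0.05 (26.4 men) to 1.3/13.8 = 0.09 (14.8 men). No such ICC is reported.

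**Illustrations at assumed prevalences** (890 men, DEFF 1.44). If control prevalence were 30%, power for .65 would be 64% and the detectable OR about 0.59. If it were 40%, the figures would be 72% and about 0.62.

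**The case against.** The strongest reply is that the gap is small where it is certain: 2.7 points at DEFF 1.4 and 3.9 at 1.44. If 1.4 were rounded from 1.35, the maximum would be 78.8%. If the odds ratio were also rounded from 0.645, it would be 80.2%. That stands as a measure of how narrow the lower-bound gap is, but closing it takes both roundings in the favourable direction and a control prevalence near 55%.

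A second reply is that 999 men were used. This is plausible: the best-case detectable OR with 999 men is 0.657, 0.653 and 0.647 at DEFF 1.4, 1.44 and 1.50. But the sentence ties the effect to sexually active men, whose number is given as 890, so on that account the wrong denominator is attached to the claim and the text still needs correction.

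A third is that weighting may explain the range. Camps were sampled with probability proportionate to size, and Data analysis says weighting is incorporated. Weights can raise a design effect, but the sample size section names only camp sizes and ICCs, and a weighting component would lower power further.

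Two stronger readings are tempting and should be resisted. A reader might infer that clustering was left out, because 890 men, 30% control prevalence and no inflation give exactly 80.0%. The article never gives 30% for this calculation and says inflation was applied. Other combinations also come to about 80%, such as 890 men with DEFF 1.2 and about 41% prevalence, so one fit proves nothing. A reader might also infer that true power is far lower, for example 57% at DEFF 1.44 using the 23.8% in the Background. That figure is women's report of physical violence in the city at large. The endpoint is camp men's own report of physical or sexual perpetration. Nor is 2.3 tied to IPV anywhere.

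**Conclusion.** The power statement is wrong as written. With 890 men, a two-sided 5% test and any design effect the protocol states, power for an IPV odds ratio of .65 is below 80% at every control prevalence: at most about 77% at DEFF 1.4, 76% at 1.44 and 56% at 2.3. This upper bound rests on equal arms and a standard two-proportion calculation with variance inflated by the design effect; it does not allow for covariate adjustment, which could add some precision but which the power statement does not invoke. The actual shortfall cannot be fixed without the control prevalence and the design effect used for IPV.

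The 80% figure can be recovered only with all 999 men, DEFF of about 1.47 or less and a control prevalence around one half, which is not the calculation described. The 1.4 to 2.3 range does not follow from the stated ICCs and camp sizes unless an unmentioned component was added. The cause of either mismatch cannot be determined from the article.

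**What to change.** In Sample size determination, state for the IPV endpoint the sample size, assumed control-arm prevalence, ICC, analysed camp size and any weighting component. Give the design effect for each endpoint separately and reconcile the 1.4 to 2.3 range with those inputs. Then replace .65 with the detectable odds ratio that follows. With 890 men it will be no closer to 1 than about 0.64 at DEFF 1.4 to 1.44; the 30% and 40% illustrations above show how it moves with prevalence, but the authors must supply the prevalence. If the 999-man total was intended, say so and reword the population. Interpret a null IPV result against the corrected value.

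The cost is a text correction and a less favourable stated detectable effect. Enrolment, design and analysis do not change.

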##### Secondary hypothesis

We hypothesize that several constructs will mediate the intervention effects. Specifically, at the individual level, men’s equitable gender role attitudes, hope, future orientation, and their perceived social support will mediate intervention effects. Additionally, at the camp level, the social cohesion as well as the structural cohesion of camp networks will mediate the effect of the intervention on the primary outcomes. We will also examine the intervention effects on secondary outcomes including unprotected sex, sexual partner concurrency, alcohol and other substance use.

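### The 539-person benchmark does not support high mediation power for the camp-level mediators, which rest on at most 60 camps, and it ignores clustering for the individual-level ones

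*Protocol article*

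**What the plan says.** In the protocol article, Sample size determination ends with one argument on mediation: "Statistical power to detect mediation is expected to be high based on the simulation results" of a cited study, in which "a total sample size of 539 was sufficient for .80 power to detect the most conservative simulated mediation effect". It makes no distinction by mediator level and mentions neither clustering nor the number of camps. The sentence just before it supplies the numbers a reader will set against 539: "Given a sample size of 890 sexually active males and 999 total males in 60 camps at our 30-month assessment".

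Elsewhere the same paragraph does allow for clustering. It gives an intraclass correlation (ICC) of "0.032 for behavioral measures" and inflates the sample size estimates "with design effects ranging from 1.4 to 2.3".

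The Overview makes the camp the unit of randomisation. Secondary hypothesis names four individual-level mediators (gender role attitudes, hope, future orientation, perceived social support) and adds that "at the camp level, the social cohesion as well as the structural cohesion of camp networks will mediate the effect of the intervention". Data analysis keeps the structural characteristics of the networks among the mediators to be assessed. It does so only if programme effects are found, using Mplus and Monte Carlo confidence intervals.

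**The concern.** A count of people is used to support a claim about mechanisms that partly operate on camps. A camp has one value of structural cohesion, and as a camp-level construct one value of social cohesion. The effect of arm on either is a comparison of 30 camps with 30, however many men are interviewed. For individual-level mediators, the design effect used for the sample size estimates is absent from the mediation sentence.

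The Background gives greater camp cohesion as one way the intervention may work, and Measures describes collecting complete network data to test it. If a camp-level indirect effect is not found, a prior statement of high power invites the reader to count that against the mechanism, when the study may have had little chance of detecting it. The primary odds ratios are not affected.

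**Working it through.** **Inputs** (Sample size determination unless stated): 60 camps, 30 per arm (Overview); average camp size 26.4; 80% enrolment; 20% attrition; 90% sexually active; 999 men and 890 sexually active men at 30 months; ICC 0.032 for behavioural measures; design effects (DEFF) 1.4 to 2.3; benchmark 539. Two-sided 0.05 is stated for the primary outcomes and used here.

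**1. The protocol's own figures.**
- 60 × 26.4 × 0.80 × 0.80 = 1013.8, against 999 stated.
- 1013.8 × 0.90 = 912.4, against 890 stated.
- Both agree within 3%. The 539 cannot be reproduced, because the effect size and test behind it are not given.

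**2. Camp-level mediators, without any assumed path.**
- Detectable arm difference at 80% power = (1.96 + 0.84) × √(2/30) = 2.80 × 0.258 = 0.72 camp-level SD.
- Selection and random assignment of camps says that camps drawn from the same proximity group went to the same set. There may therefore be fewer than 60 independent units; the number is not given.

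**3. Camp-level mediators, with an assumed path.**
- Assumption: two equal standardised paths, both required to be significant, with 80% power at 539 independent people.
- Power per path ≈ Φ(atanh(r) × √(n − 3) − 1.96). Solving power² = 0.80 at n = 539 gives r = 0.138 (0.894 per path).
- At n = 60 the same path has power 0.18. Mediation needs both paths, so 0.18 is a ceiling.
- A simulation of 60 camps of 17 men (continuous outcome, cluster-robust second path, 4,000 runs) also gave 0.18.
- Range: with the second path held at 0.138 and outcome ICC 0.032, simulated power is 0.59, 0.81 and 0.86 for a first path of 0.3, 0.4 and 0.5. The first path alone needs about 0.35 for 80% power.

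**4. Individual-level mediators.** Effective N = N/DEFF.

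| Men | DEFF 1.4 | DEFF 2.3 | Largest DEFF that keeps 539 |
|---|---|---|---|
| 999 | 714 | 434 | 999/539 = 1.85 |
| 890 | 636 | 387 | 890/539 = 1.65 |

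- With ICC 0.032 and 999/60 = 16.65 men per camp, DEFF = 1 + 15.65 × 0.032 = 1.50. Effective N is then 999/1.50 = 666 or 890/1.50 = 593, both above 539.
- At the assumed path of 0.138, applying the design effect to both paths gives power 0.92 (714), 0.88 (636), 0.67 (434) and 0.60 (387).
- The simulation, in which the mediator-to-outcome path also draws on differences between men in the same camp, gives 0.98 (ICC 0), 0.94 (ICC 0.032) and 0.81 (ICC 0.081, which is DEFF 2.3 with 17 men).

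**The case against.** The strongest reply is that most of the claim may survive. Four of the six mediators are individual-level. At the protocol's behavioural ICC the effective number stays above 539, and simulated power is 0.81 to 0.94 for ICCs from 0.032 to 0.081. This stands. A reader might infer that clustering makes the claim false for every mediator, but the documents do not show that: the design-effect range falls on both sides of 539, and no ICC is given for any mediator.

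A second reply concerns scale. Social cohesion is built from five items answered by individual men, and camp means vary less than individuals do. A path of 0.138 is an arm difference of about 0.28 individual SD. With 16.65 men per camp and assumed ICCs of 0.032, 0.10 and 0.20, that equals 0.93, 0.71 and 0.56 camp-mean SD, with first-path power of about 94%, 77% and 57%. On the same basis, 0.72 camp-mean SD is about 0.22 to 0.36 individual SD. This also stands: the 18% is not a general result for social cohesion. It does not help structural cohesion, which has no individual scale. A reader might go further and put both paths on 60 units, which gives power of about 3%. That is not supported either, because the outcome is measured on individual men.

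Third, mediation is a secondary hypothesis, assessed only if programme effects appear, and intervals are already planned. Nothing in the article says a null mediation result will be read as evidence against a mechanism. This limits the importance of the point, but an unqualified statement of high power still needs correcting.

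Lastly, the article does not say that the 539 were independent observations, nor does it compare 539 explicitly with 890 or 999. Both are inferences, though those are the only sample sizes the paragraph offers for comparison.

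**Conclusion.** The concern holds in part.

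- **Camp-level mediators:** the benchmark does not support high power. The limit of at most 60 units and the 0.72 SD detectable difference follow from the design alone (normal approximation, camps treated as independent). The ceiling of about 18% depends on the back-solved path of 0.138 being a standardised path across camps. It is clearest for structural cohesion and may be too pessimistic for averaged social cohesion.
- **Individual-level mediators:** the claim is unsupported as argued, not shown false. It is met if DEFF is at most 1.65 (890 men) or 1.85 (999 men), within a stated range of 1.4 to 2.3.

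The simulations used a continuous outcome. The trial's outcomes are binary, which would probably lower power. This is an inexpensive correction to a statement about a conditional secondary analysis, and the primary comparison is untouched.

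**What to change.** - Remove the blanket statement that mediation power is expected to be high.
- For social and structural cohesion, state that the arm-to-mediator path rests on at most 60 camps, and fewer independent units if grouped camps were assigned together. Give the detectable difference (about 0.72 camp-level SD), and say that a null camp-level indirect effect is not evidence against the mechanism.
- For the individual-level mediators, compare 539 with the design-effect-adjusted number over the stated range (387 to 714), and say where it is and is not reached.
- Account for camp clustering in the Mplus mediation model, with camp as the unit for the arm-to-mediator path of camp-level mediators.

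The cost is a few sentences and a model specification in software already named. No data collection or primary analysis changes. The drawback is that the stated mediation power becomes less favourable.
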